## Assignment of interventions: Blinding

### Who will be blinded {17a}

In keeping with clinical trials where interventions cannot be blinded, we will ensure that data will be collected independently from those conducting analysis (blinded to group allocation) to minimize bias. Mothers, staff, and research nurses and assistants completing data collection will not be blinded to whether the infant has been randomly assigned to SSC condition or the 24% oral sucrose condition. All individuals carrying out data analysis will be blinded to group assignment. Additionally, EEG data analysts will have no prior knowledge of study groups and assignment. Close up video of the infants face during the painful procedure with no sound will be recorded to ensure that coders will be blinded to all aspects of group allocation and study purpose.

### Procedure for unblinding if needed {17b}

It is not anticipated that there will be a need to unblind the data prior to analyses.

## Data collection and management

### Plans for assessment and collection of outcomes {18a}

Set-up of EEG equipment, video recording, and physiological monitoring is anticipated to take 20–30 min. Baseline measurements (BL1 and BL2, 2 min each), stabilization in SSC after transfer (15 min), and heel lance procedure (three to 5 min) is estimated to take 20–25 min for a total data collection period of 40–60 min. Infants will be followed until completion of a regularly scheduled heel lance procedure.

### Plans to promote participant retention and complete follow-up {18b}

Follow-up is completed within minutes of finishing the procedure; therefore, it is unlikely there will be missing data due to loss to follow-up.

### Data management {19}

Collection of both bio-behavioural data and pain-specific ERPs on EEG have been previously demonstrated in clinical trials with this patient population [16, 57]. A challenge that may be encountered during data collection is loss of physiologic data (e.g. heart rate and electrophysiologic measurements) due to equipment failure or movement artefact. EEG procedures will be employed to control for and limit loss due to artefact. Research personnel experienced in EEG techniques will be present during data collection to monitor data recordings and make prompt adjustments in the instance of any recording malfunctions to limit data loss.

### Confidentiality {27}

Study participants will not be identified in any reports or publications of this research. Participant study data and videotapes will be kept in a locked file cabinet in a locked office at IWK Health. All data will have participant names removed and identified only by a code. The code will be kept in a locked file cabinet in a locked office at IWK Health. Study records will be kept for a minimum of 10 years. Only the staff involved in the research will see them. Members of the IWK Research Ethics Audit Committee or delegates of the Nova Scotia Health Research Foundation may look at the records to ensure the study is being conducted properly.

### Plans for collection, laboratory evaluation and storage of biological specimens for genetic or molecular analysis in this trial/future use {33}

N/A: No biological specimens were collected as part of this trial.

## Statistical methods

### Statistical methods for primary and secondary outcomes {20a}

Descriptive statistics will be used to summarize baseline characteristics using the Statistical Package for the Social Sciences (SPSS, IBM Corporation, Armonk, NY, USA). Student t tests and chi-square tests will be used, as appropriate, to assess potential differences across intervention groups at baseline.

#### Noxious-related brain activity

Data from the EEG recordings will be processed and statistically analysed using the MNE (v. 0.24.0) [58], and the event-related potential (ERP) Principal Component Analysis (PCA) Toolkit (v. 2.76) [59] in MATLAB (MathWorks Inc., Natick, MA, USA). For artefact detection and correction, a copy of the continuous EEG data will be bandpass filtered using MNE from 1 to 30 Hz using a zero-phase finite impulse response filter with a hamming window. Since Cz is provided as the default reference channel in the EGI system, all EEG data will be re-referenced to Fz (E17 in the EGI system). This will retain data recorded from Cz, an area with reported pain-related activity in both infants [14–16] and adults [43]. Fz has also previously used as the reference electrode in neonatal pain research [60].

This raw, continuous EEG data will then be segmented into epochs time-locked to the event markers of experimental interest (including noxious and non-noxious stimuli), ranging from 500 ms prior to each event marker to 1000 ms after, with each segment normalized by subtracting the mean amplitude value over the segment from each time point (effectively centering each segment at 0 µV). Epochs will be excluded if they contain movement artefacts on electrode Cz. Any epochs containing peak-to-peak signal amplitudes exceeding 150 µV will be considered contaminated with movement artifacts [60]. The data reduction technique of x (PCA [59] will be applied to the data at electrode Cz to identify mathematically independent components of the waveform. The resulting principal components (PCs) represent systematic variation in the amplitude of the EEG signal at different time points across the EEG tracing. The latency and amplitude of the generated principal components will be examined and the PC corresponding to a N420-P560 will be retained for subsequent phases of the analysis. Four principal components will be examined: two PCs for the SSC group (PC for non-noxious control stimulus, PC for noxious heel lance) and two PCs for the sucrose group (PC for non-noxious control stimulus, PC for noxious heel lance). Two-way analysis of variance (ANOVA) test will be run to assess the effect of stimulation type (non-noxious control stimulus, noxious heel lance) and treatment (SSC and sucrose) on the peak amplitude of the principal components. With this analysis, it is possible to assess if (1) exposure to heel lance produces a pain-specific component and (2) if the magnitude of this component varies between intervention groups [14, 61]. If there are identified differences between groups in any potential confounding variables (i.e. prior pain exposure, infant sex) analysis of covariance (ANCOVA) will be utilized to adjust for the potential effect of these covariates.

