### Outcomes {12}

#### Noxious-related brain activity

Noxious-related brain activity will be measured from a pain-related event-related potential [14–16, 41] induced by a clinically required heel lance measured using a dense-array neonatal EEG recording. The primary outcome attributed to the clinically required heel lance will be a noxious-related N420-P560 event-related potential (ERP) which will specifically be examined and isolated at electrode Cz as previous research has reported pain-related activity at this site in both neonates [14, 16, 42] and adults [43].

The EEG data will be recorded using a 32 channel HydroCel Geodesic Sensor Net connected to a GES 400 EEG system (EGI, Eugene, OR, USA). Electrodes will be submerged for 5 min in a solution of warm water and infant shampoo. Electrode impendences will be checked to ensure they are below the impedance threshold of 100 kΩ. NetStation Acquisition software (version 5.2.0.2) will be used for recording of EEG activity from 0.5 to 30 Hz with a sampling rate of 1000 samples per second and a conversion of 24 bit. For all infants, regardless of randomization, data collection will begin with a continuous recording of a one-minute baseline of all outcome measures while the infant is resting in their incubator or cot (BL1). Following this, a non-noxious (NN1) control stimulus will be applied to the infant’s foot to capture a baseline response on EEG to a non-painful event. This non-noxious (sham) stimulus will consist of placing the heel lance against the foot and rotating it 90 degrees, so that when the lance is released it mimics the sensation of the heel lance procedure without the associated tissue-breaking and pain. The infant will then be placed in their assigned intervention group and will be re-exposed to the non-noxious control stimulus, followed by the clinical heel lance.

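### The primary EEG variable is defined in two incompatible ways: one retained N420-P560 component, or a separate component for each arm and stimulus

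*Protocol article*

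**What the plan says.** Outcomes {12} of the protocol article names one primary variable: "The primary outcome attributed to the clinically required heel lance will be a noxious-related N420-P560 event-related potential (ERP", taken at electrode Cz. Statistical methods {20a}, under Noxious-related brain activity, then describes how it is obtained:

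- PCA "will be applied to the data at electrode Cz to identify mathematically independent components of the waveform". This sentence mentions no split by arm or stimulus.
- One component is kept: "The latency and amplitude of the generated principal components will be examined and the PC corresponding to a N420-P560 will be retained".
- Components are then assigned to arms and stimuli: "Four principal components will be examined: two PCs for the SSC group (PC for non-noxious control stimulus, PC for noxious heel lance". The other arm is given a matching pair.
- A two-way ANOVA tests the effect of stimulus and "treatment (SSC and sucrose) on the peak amplitude of the principal components".
- The stated purpose of that ANOVA returns to the singular: whether the size of one component differs between the groups.

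Who will be blinded {17a} adds: "All individuals carrying out data analysis will be blinded to group assignment".

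**The concern.** A sound analysis of this kind has one component and four sets of scores on it. The only sentence that links components to arms and stimuli gives four components, one per cell. The ANOVA is then worded as a comparison of components, not of scores on one component.

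A principal component's loading depends on the variance of the data it is extracted from. Separate extraction therefore gives each arm its own weights and its own scale. The two arms would be compared on different variables, and a difference, or its absence, could come from the extraction and not from the infants' responses. This is the trial's only primary comparison.

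**Working it through.** **The plan's own figure.** The article gives no mean or SD for the ERP, so 63 per group can be recomputed only from its PIPP-R inputs (difference 1, SD 2, 5% taken as two-sided, 80% power): n = 2 × (1.960 + 0.842)² × 2² / 1² = 62.8, so 63. This agrees. It does not bear on the point, but it supplies the n used below.

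**The two readings side by side.** Singular: PCA on the Cz data, one component retained, one component's magnitude compared between groups. Plural: four components, two per arm, and ANOVA on the components' peak amplitudes. Nothing says that a separate PCA is run in each cell. Nothing says that one common loading is scored in all four.

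**Algebra if each cell has its own PCA.** Let infant i's epoch be x_i = a_i·T + e_i, where T is the N420-P560 shape. Let v be the loading and r(v) its peak-to-peak range. The score amplitude is (x_i·v)·r(v).

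1. *Common v:* the expected arm difference is (ā₁ − ā₂)·(T·v)·r(v). It is zero when the mean responses are equal.
2. *Separate v, not centred:* the expected difference is ā₁·(T·v₁)·r(v₁) − ā₂·(T·v₂)·r(v₂). With ā₁ = ā₂ it is zero only if the two loadings happen to agree. A test that treats v₁ and v₂ as fixed also ignores their sampling error.
3. *Separate v, scores centred within cell:* each cell's mean score is ((x̄ − x̄)·v)·r(v) = 0. The arm difference is zero whatever the truth.

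**Simulation.** The assumptions here are not from the article. There were 63 infants per arm, mean response 20 in both arms under no effect, 14 against 20 for a 30% reduction, noise 10 and background components of size 6 (arbitrary units). The best N420-P560 match among the first six components was taken, and arms were compared on the heel-lance epoch by a two-sided 5% t-test. There were 1000 runs per null scenario, so error around 5% is √(0.05 × 0.95 / 1000) = 0.7 points.

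| Null scenario | Separate PCA, uncentred | One pooled PCA, uncentred |
|---|---|---|
| Same background in both arms | 6.1% | 5.5% |
| Late background 6 vs 12 | 8.3% | 4.5% |
| Slow background 6 vs 14 | 10.6% | 6.5% |
| Early background 6 vs 12 | 4.3% | 4.7% |
| Same background, noise 20 | 15.4% | 5.5% |
| Same background, mean 8, noise 15 | 15.6% | 5.0% |

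The first four scenarios were also run with centring. Separate PCA centred within cell rejected in 0% of runs under no effect and in 0% under a true 30% reduction. Pooled centred PCA rejected in 4.5% to 5.7% under no effect. Pooled PCA detected the 30% reduction in 58% to 79% of runs (500 per scenario, both centring choices).

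Two further sets of runs used other assumed SDs and noise levels. Where loadings came from each arm's centred data but were applied to raw epochs, type I error was 6.5% to 71%. Uncentred separate PCA gave 4% to 24%, with one very noisy scenario at 41%. Pooled PCA gave 2.5% to 7%.

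**The case against.** The strongest reply is that the four-component sentence is only loose wording for one component summarised in four cells. It follows the retention step, precedes a 2 × 2 ANOVA with exactly those cells, and says that components will be examined, not derived. The singular wording before and after supports this. The article is also a condensed account: it names the PCA toolkit and version, and the input matrix, centring and scoring rule commonly belong in an analysis plan, which is not shown here.

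Much of this stands. A reader might infer that four separate decompositions are planned and that false differences will follow. The text does not establish the first. The second is only one possible outcome: error may stay near nominal, rise well above 5%, or the contrast may vanish. A reader might also expect an arm with less between-infant spread to show a spuriously smaller peak. With an SD of 6 against 4.2, one convention gave an arm ratio of 0.75 with no mean difference, but uncentred extraction gave 0.98 to 1.02.

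Nor does the text support a claim that analysts' blinding is broken. Data split under coded labels are compatible with {17a}, and choosing components by eye within each arm is not described. Noise that differs by arm is conjecture too: the article gives no noise figures by arm, excludes epochs above 150 µV peak to peak, and has staff watching the recordings.

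The reply does not remove the inconsistency. The article does not leave the number and assignment of components to a later document. It states them, and in a form that conflicts with the sentences around it.

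**Conclusion.** The point holds as an inconsistency in the definition of the primary variable. One of the two definitions is usable, and the other, if carried out with separate decompositions, does not give a valid treatment contrast. That the contrast is forced to zero under within-cell centring follows from algebra and needs no assumption about the data. The size of any type I error inflation does not follow from the article. In the main simulation it ran from none to about three times nominal (4.3% to 15.6%), and in other runs it was higher still under a different centring convention. These rates depend on assumed waveforms, noise and selection rule, and on a t-test standing in for the ANOVA. One pooled PCA with common loadings stayed near 5% throughout (2.5% to 7%). Because this is the sole primary comparison, the definition should be settled before the data are analysed.

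**What to change.** Replace the four-component sentence in Statistical methods {20a} with a statement that:

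- one PCA is run on all Cz epochs pooled across infants, arms and stimuli, with group labels removed;
- one N420-P560 component is selected by a fixed latency or template rule, before unblinding;
- every infant and stimulus is scored with that same loading and scaling, with the centring convention stated;
- those scores, being four cells of one component, enter the primary analysis.

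The cost is a few sentences and a change to the analysis script. No new data are needed. If a pooled decomposition was always intended, only the wording changes.

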### Sample size {14}

Using a priori data [15], we will require 63 participants per group (total sample size of 126 for the two groups) to detect a 30% reduction in amplitude of the pain-specific ERP on EEG during the clinically required heel lance. The sample size calculation accounts for multiple testing across intervention groups and is based on a type I error probability of 5% and power of 80% [54]. Sixty-three participants per group also allows us to detect the smallest clinically important difference of one on the PIPP-R scale, with a standard deviation of two, considered a clinically relevant difference between the active interventions of SSC and 24% oral sucrose [55].

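### Each infant has two sham responses but the primary ANOVA has one unspecified sham level, and neither the pre-treatment sham nor the GA stratum is a prespecified covariate

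*Protocol article*

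**What the plan says.** **Recordings** (Outcomes {12}, Noxious-related brain activity). After a resting baseline in the incubator or cot, "a non-noxious (NN1) control stimulus will be applied to the infant’s foot to capture a baseline response on EEG to a non-painful event". The infant is then placed in the assigned condition and "will be re-exposed to the non-noxious control stimulus, followed by the clinical heel lance". That makes three evoked responses per infant: NN1, a second sham under treatment, and the lance.

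**Analysis** (Statistical methods {20a}, Noxious-related brain activity). Four principal components are to be examined, two per arm: "two PCs for the SSC group (PC for non-noxious control stimulus, PC for noxious heel lance"), and the same pair for sucrose. The ANOVA is to "assess the effect of stimulation type (non-noxious control stimulus, noxious heel lance) and treatment (SSC and sucrose) on the peak amplitude" of the components. The section says this can show whether the lance produces a pain-specific component and whether its size differs by arm.

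**Covariates** (same section). Adjustment is conditional: "If there are identified differences between groups in any potential confounding variables (i.e. prior pain exposure, infant sex"). NN1 is not named. The GA stratum is a stratification factor in Sequence generation {16a} and the covariate for PIPP-R under Pain intensity, but it is not in the primary model.

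**Hypothesis and size.** The primary hypothesis is lower ERP amplitude during the lance with SSC. Sample size {14} aims "to detect a 30% reduction in amplitude of the pain-specific ERP on EEG during the clinically required heel lance", with "type I error probability of 5% and power of 80"% and 63 infants per group.

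**The concern.** Three recordings do not fit a two-level stimulus factor unless one sham is dropped or the two are pooled, and the section does not say which. The choice changes what the arm-by-stimulus term estimates.

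- **Lance minus NN1.** NN1 precedes treatment, so the arm difference in this contrast is the total treatment effect on the lance response. It includes any general effect of SSC on touch responses or background EEG, so it is not pain-specific.
- **Lance minus in-treatment sham.** Both responses are recorded under treatment, so an additive general damping cancels. What remains is the effect beyond that damping. If treatment also lowers the sham response, the contrast shrinks and loses power.

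The second cost is precision. NN1 is the same kind of measurement, in the same infant, before treatment. It could reduce the error variance of the between-arm comparison, but as written it enters only if someone judges the arms to differ on it. Choosing covariates from observed imbalance also leaves the final primary model open until the data have been seen.

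**Working it through.** **Inputs.** From Sample size {14}: n = 63 per arm, alpha 5%, power 80%, and for PIPP-R a difference of 1 with SD 2. Two-sided testing is assumed; it reproduces the stated n. The within-infant correlation r between responses is not given, so 0.3–0.5 is assumed. All three responses are given unit SD.

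**1. The plan's own figure.** n = 2(1.960 + 0.842)² / (1/2)² = 62.8, so 63 per arm, as stated. With the noncentral t, power at n = 63 is 79.5%.

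**2. Implied effect on the ERP.** No ERP mean or SD is given. The standardised effect detectable with 63 per arm is (1.960 + 0.842) × √(2/63) = 0.499, about 0.5 SD. A 30% reduction then implies an SD of about 0.30/0.499 = 60% of the mean amplitude.

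**3. Lance amplitude adjusted for NN1 (ANCOVA).** The residual SD is √(1 − r²), so the effect becomes 0.5/√(1 − r²). The equivalent unadjusted size is 63(1 − r²).

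| r | Adjusted effect | Power | Equivalent n per arm |
|---|---|---|---|
| none (unadjusted) | 0.500 | 79.5% | 63 |
| 0.3 | 0.524 | 83.1% | 57 |
| 0.4 | 0.546 | 86.0% | 53 |
| 0.5 | 0.577 | 89.5% | 47 |

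Any gain from the GA stratum is not counted.

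**4. Lance minus a sham.** The SD of the difference is √(2(1 − r)), which is 1.183 at r = 0.3 and 1.000 at r = 0.5.

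| Contrast | r = 0.3 | r = 0.5 |
|---|---|---|
| Lance minus NN1, lance effect 0.5 SD | 65% | 80% |
| Lance minus in-treatment sham, sham unaffected by treatment | 65% | 80% |
| Lance minus in-treatment sham, sham lowered by half the lance effect (net 0.25 SD) | 22% | 29% |

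**5. Does NN1 help the lance-minus-in-treatment-sham contrast?** With equal correlations, Cov(NN1, lance − second sham) = r − r = 0. NN1 explains none of that difference, so the gain in step 3 does not carry over.

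**6. A general SSC effect only.** Suppose SSC lowers every evoked response by 0.2 SD and has no effect specific to the noxious part. Lance minus NN1 is then significant in 16% (r = 0.3) to 20% (r = 0.5) of trials, and lance minus in-treatment sham in 5%. A plain comparison of lance amplitude is significant in 20%, because lance amplitude really is 0.2 SD lower.

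**The case against.** The strongest reply is that the choice of epoch and baseline adjustment are details for a full protocol or SAP, and that the timeline figure, which is not available, may settle them. That has some force for the covariate. It has less for the stimulus factor, because the analysis section itself fixes four components and two stimulus levels, and these do not match the recordings described under Outcomes.

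A second reply is that randomisation balances NN1 in expectation, so lance minus NN1 is an unbiased estimate of the treatment effect on the lance response. That stands. The limit is on interpretation, because the result would not be pain-specific. Retaining only the N420–P560 component may reduce a general touch effect, but nothing in the protocol shows that it removes it.

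Three stronger readings are tempting and are not supported.

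- **That using NN1 as the sham inflates type I error, at 16–20% against 5%.** The primary hypothesis concerns amplitude during the lance, and in that scenario the amplitude truly falls. The figure is power for a real but non-specific effect, not a false-positive rate.
- **That the in-treatment sham is simply the right comparator.** It is a trade-off: power can drop to 22–29% (step 4).
- **That NN1 certainly goes unused.** The two shams might be pooled. What is certain is that NN1 has no level of its own and is not a named covariate.

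**Conclusion.** The point holds in two parts. First, the recordings and the primary model do not match, and the meaning of the arm-by-stimulus term depends on a choice the protocol does not make. Second, prespecifying NN1 and the GA stratum as covariates for lance amplitude is an improvement available from data already collected. It is worth roughly 4 to 10 percentage points of power at 0.5 SD, equivalent to about 6 to 16 infants per arm.

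The size rests on the assumed correlation of 0.3–0.5, the 0.5 SD effect implied by n = 63, two-sided testing and complete data. With a correlation near zero the gain disappears, but almost nothing is lost. The gain applies to the between-arm comparison of lance amplitude and should not be quoted for the lance-minus-in-treatment-sham contrast. This is a change that should be made; it does not show that the planned trial is invalid.

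**What to change.** In Statistical methods {20a}, Noxious-related brain activity:

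1. For the primary hypothesis, compare SSC with sucrose by ANCOVA on heel-lance N420–P560 amplitude, with NN1 amplitude and GA stratum as prespecified covariates whether or not imbalance is seen. State how an NN1 epoch rejected for artefact is handled, so that a missing covariate does not remove the infant.
2. State which sham recording forms the non-noxious level, or that the two are combined, and that the arm-by-stimulus term is tested within infant.
3. State the reading that goes with the choice. With NN1, the term is the total treatment effect on the lance response and is not to be called pain-specific. With the in-treatment sham, it is the effect beyond general damping, with less power if treatment also lowers the sham response.

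The cost is analysis wording, settled before unblinding. Both sham responses and the stratum are already collected for every infant.

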### Hypotheses

#### Primary

Infants randomized to the SSC condition, when compared to infants randomized to the 24% oral sucrose condition, will demonstrate a lower amplitude pain-specific event-related potential during a clinical (heel lance) noxious stimulus.

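### The primary two-way ANOVA names no within-infant error term and no deciding term for the between-arm lance difference; for a lance-only effect with equal SDs, each ordinary treatment term has about 51% power

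*Protocol article*

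**What the plan says.** Outcomes {12}, Noxious-related brain activity: every infant first receives a sham stimulus at rest (NN1). Once in the assigned intervention, the infant is "re-exposed to the non-noxious control stimulus, followed by the clinical heel lance". Sham and lance responses therefore come from the same infant, at the same electrode, in one session.

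Statistical methods {20a}, Noxious-related brain activity: "Four principal components will be examined: two PCs for the SSC group" (one for sham, one for lance), and the same for sucrose. Then: "Two-way analysis of variance (ANOVA) test will be run to assess the effect of stimulation type (non-noxious control stimulus, noxious heel lance) and treatment", with peak component amplitude as the response. The section says this will show whether the lance produces a pain-specific component and "if the magnitude of this component varies between intervention groups". It names no infant effect, repeated-measures structure or deciding term, and does not say which of the two sham exposures enters the model. ANCOVA appears only as a fallback if the groups differ on potential confounders.

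Hypotheses, Primary: infants in SSC "will demonstrate a lower amplitude pain-specific event-related potential during a clinical (heel lance) noxious stimulus", compared with sucrose.

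Sample size {14}: the trial needs "63 participants per group (total sample size of 126 for the two groups) to detect a 30% reduction" in ERP amplitude during the lance, with 5% type I error and 80% power. No ERP mean, SD or test is given.

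**The concern.** Two separate problems arise in the one analysis that decides the trial.

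- **Error term.** Stimulation type varies within infants. An ordinary two-way ANOVA pools all amplitudes into one residual as if they were independent. With positive within-infant correlation, that residual is too small for comparing arms on the infant average and too large for comparing arms on the lance-minus-sham difference.
- **Target.** The hypothesis is a between-arm difference at the lance. The treatment main effect averages sham and lance, so it halves an effect confined to the lance. The interaction compares lance-minus-sham differences, whose variance is 2(1−ρ) times that of a single response. That is double at ρ = 0 and equal at ρ = 0.5. Neither is the comparison that the sample size appears to rest on.

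At stake are a false-positive rate that could roughly double if the main effect is read, or a real lance effect missed about half the time while 80% power is reported. With no deciding term named, either of two different tests could be presented as the primary result. The main effect could also be significant because SSC changes the response to the painless sham.

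**Working it through.** **Inputs.** From Sample size {14}: n = 63 per arm, α = 5% (two-sided assumed; sidedness is not stated), power 80%; for PIPP-R, a difference of 1 with SD 2. Assumed because the documents do not give them: within-infant correlation ρ between the two responses in the ANOVA, the ratio of sham SD to lance SD, and any treatment effect on the sham.

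**Reproducing 63.** n = 2(1.96 + 0.842)²/d². With d = 1/2 = 0.5, n = 2 × 7.85/0.25 = 62.8, so 63 per arm. This follows from the PIPP-R inputs. The ERP calculation cannot be reproduced without an SD. If 63 per arm gives 80% power for a 30% reduction in a two-group comparison, the SD is 0.30/0.5 = 60% of the mean, that is d = 0.5.

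**Base case: lance-only effect d = 0.5, equal SDs.**

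- Direct lance comparison: z = 0.5 × √(63/2) = 2.81; power Φ(2.81 − 1.96) = 80%.
- Ordinary ANOVA main effect: effect 0.5/2 = 0.25, nominal standard error √(1/63) = 0.126; z = 1.98, power about 51%.
- Ordinary ANOVA interaction: effect 0.5, nominal standard error √(4/63) = 0.252; z = 1.98, power about 51%.

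Both powers stay near 51% at every ρ from 0 to 0.8, because the expected statistic sits almost on the critical value.

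**Type I error of the ordinary ANOVA.** Main effect: 2[1 − Φ(1.96/√(1+ρ))]. Interaction: 2[1 − Φ(1.96/√(1−ρ))].

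**Power with correct within-infant error.** Main effect: z = 1.984/√(1+ρ). Interaction: z = 1.984/√(1−ρ).

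| ρ | Ordinary: main type I | Ordinary: interaction type I | Ordinary: power, each term | Repeated measures: main power | Repeated measures: interaction power |
|---|---|---|---|---|---|
| 0 | 5% | 5% | 51% | 51% | 51% |
| 0.3 | about 8.5% | 1.9% | 51% | 41% | 66% |
| 0.5 | about 11% | about 0.5% | 51% | 37% | 80% |
| 0.7 | about 13% | <0.1% | 51% | 33% | 95% |

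Simulation of the ordinary ANOVA (20,000 trials per setting) agrees: at ρ 0.3 and 0.5, main-effect type I error was 8.3% and 11.0%, and interaction type I error 1.9% and 0.7%. Power was 50% to 52% for both terms.

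**Departures from the base case, ordinary ANOVA.**

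- Sham SD half the lance SD: interaction power 71% (ρ 0), 76% (0.5), 82% (0.8).
- Sham SD a quarter of the lance SD: interaction power 77% (ρ 0), 81% (0.5). Main-effect type I error at ρ 0.3 falls to about 6.5%.
- Treatment lowers the sham response equally: main-effect power 94% to 98%. Half as much: 78% to 84%.

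**Proposed ANCOVA.** With correlation r between lance and NN1, the effective difference is 0.5/√(1−r²). Power is 80% at r = 0, 84% at 0.3 and 90% at 0.5. This r is not the same quantity as ρ if the ANOVA uses the second sham.

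**The case against.** - **Two-way counts factors, not error terms.** A repeated-measures ANOVA with these two factors is also two-way, and a condensed article may leave the error structure to an analysis plan that is not shown. This stands: the error-rate figures apply only if the ordinary version is run and ρ is above 0. It does not settle the matter. Under the repeated-measures reading the main effect has only 37% to 41% power at ρ 0.3 to 0.5, the interaction 66% at ρ 0.3, and the deciding term is still unnamed.
- **Pain-specific may mean lance beyond sham.** On that reading the interaction is the natural test. This is a fair reading of the phrase. But the hypothesis and the sample size both place the amplitude at the lance, and an interaction test needs 126, 88, 63 or 38 per arm at ρ 0, 0.3, 0.5 or 0.7. The plan gives no ρ.
- **The basis of the ERP sample size is inferred.** No ERP SD or test is stated, and the section says the calculation allows for multiple testing. This stands: d = 0.5 is an implication of 63 per arm, not a documented input.
- **Equal SDs are debatable.** The lance, not the sham, is expected to produce the component, so the sham SD may be smaller. This stands, and it softens both the power loss and the type I inflation.

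A reader might infer that the plan definitely treats the paired responses as independent, that its error rates are therefore wrong, and that no treatment test can have 80% power. The documents do not support that. They do not state independence, and several settings above reach 80%.

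**Conclusion.** The point holds in conditional form. The sole primary analysis involves a within-infant factor but names no within-infant error, and it does not name the term that tests the hypothesised arm difference at the lance.

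For a lance-only effect of d = 0.5 with equal SDs, each ordinary treatment term has about 51% power against 80% for the direct lance contrast. If an ordinary ANOVA is run with ρ between 0.3 and 0.5, the main effect is anti-conservative (about 8.5% to 11%) and the interaction conservative (about 1.9% to 0.5%). At ρ = 0 the error rates are correct. A repeated-measures model makes them valid at any ρ, and its interaction reaches 80% power at ρ of 0.5 or above. A smaller sham SD raises interaction power, and a treatment effect on the sham raises main-effect power. None of these quantities is in the documents, so the 80% claim is unsupported for the ANOVA as described rather than shown to be false in every case.

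It should be settled before the single final analysis.

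**What to change.** Replace the two-way ANOVA as the primary test with the between-arm difference in lance amplitude, from a linear model with arm, GA stratum and the infant's pre-intervention sham amplitude (NN1). Prespecify a method for a missing baseline covariate, so that infants whose NN1 epoch is rejected for artefact stay in the analysis. The gain to about 84% or 90% power applies only if lance amplitude correlates with NN1 at 0.3 or 0.5; with no correlation, power is about 80%.

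An alternative, not an equivalent, is a mixed model with an infant effect and a predeclared arm contrast at the lance. Without baseline adjustment it has about 80% power under the same assumptions.

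Report the arm-by-stimulus interaction, tested against within-infant error, as the supportive test of pain specificity, and state which sham exposure it uses.

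The cost is analysis wording only. All the data are already being collected, and the article describes a trial still recruiting with no interim analysis.
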